## Background

Breastmilk is a unique food tailored to meet the nutritional, immunological and developmental needs of human infants [1]. The health benefits of breastfeeding are realized in a dose-response relationship to the degree of exclusive breastfeeding, particularly in early infancy [1]. The World Health Organization and Health Canada recommend that all infants be exclusively breastfed (i.e. receive only breastmilk and essential vitamins, minerals and medicines) for the first 6 months of life [2, 3]. However, achievement of this goal remains elusive. Globally, only 42% of infants under 6 months of age are exclusively breastfed [4]. National data show that 90% of Canadian mothers initiate breastfeeding, but nearly half discontinue within the first 6 months and only 32% exclusively breastfeed for 6 months [5]. Exclusive breastfeeding is compromised by a variety of practices, particularly formula supplementation and early introduction of solids [6, 7]. Exclusive breastfeeding duration is lower among vulnerable women in Canada, such as those with lower income and education levels, adolescents, single parents and those living in food insecure households [8–12]. Global systematic review evidence indicates that immigrant women are more likely to initiate and continue breastfeeding than their native-born counterparts, likely reflecting social norms regarding breastfeeding in many countries of origin, but exclusive breastfeeding is a universal challenge [13].

Two key contributors to both early cessation and non-exclusive breastfeeding are the perception of insufficient breastmilk supply and unresolved breastfeeding difficulties [14–17]. Access to skilled lactation support in the early postpartum period can be vital to addressing these concerns and supporting women to achieve their breastfeeding goals [18]. Underlying these concerns is breastfeeding self-efficacy, a construct drawn from Bandura’s social-cognitive theory and defined as a woman’s confidence in her ability to breastfeed her new baby [19]. Women with high breastfeeding self-efficacy are better able to overcome common challenges and continue breastfeeding [19]. Theory-based postpartum lactation support interventions have been shown to improve breastfeeding self-efficacy, duration and exclusivity [20, 21].

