## Methods

### Study design and hypothesis

We will conduct a pre/post intervention study with clients of two CPNP sites in Toronto. Prospectively collected data on infant feeding practices over the first 6 months and breastfeeding self-efficacy scores will be compared between participants who give birth before and after initiation of the lactation support intervention. This quasi-experimental design was chosen as it would not be either ethical or feasible to randomize clients at these community programs targeting vulnerable women to intervention and control groups.

The primary outcome is exclusive breastfeeding at 4 months postpartum. We hypothesize that CPNP clients with access to our lactation support intervention will be more likely to exclusively breastfeed their infants at 4 months postpartum compared with those in the pre-intervention group, and that this effect will be mediated by higher breastfeeding self-efficacy scores. Secondary outcomes are duration of any breastfeeding; duration of exclusive breastfeeding; timing of introduction of breastmilk substitutes (formula); and timing of introduction of solids. We will also assess the rates of any and exclusive breastfeeding and use of expressed breastmilk at each data collection time point up to 6 months postpartum.

Although 6 months is the recommended duration of exclusive breastfeeding, we chose 4 months for the primary outcome analysis as we anticipate that our intervention will improve exclusive breastfeeding primarily by building breastfeeding skills and addressing difficulties in the early postpartum period. Exclusive breastfeeding is frequently compromised after 4 months through early introduction of solids [6, 9], but this practice is less amenable to influence by lactation support provided earlier in the postpartum period.

Monitoring data will be collected and analyzed to determine the reach, uptake and fidelity of the intervention.

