### Intervention description

Clients registered prenatally in either the GST or HB program who give birth during the intervention period and live in the city of Toronto will have access to in-home lactation support from an IBCLC. This service will be offered pro-actively in the early postpartum period, but will be available throughout the first 6 months. A Research Coordinator will oversee intervention delivery, and professional interpreter services (in-person or by telephone) will be used for communication with non-English speaking women.

The Research Coordinator will attend both weekly programs and approach eligible prenatal clients individually to explain the service, provide her contact details, and record the contact information of clients who are interested. Clients will be encouraged to contact the Coordinator if they need lactation support, but the Coordinator will also pro-actively telephone interested clients around the time of birth to offer the IBCLC support and make the arrangements with the IBCLCs as required. IBCLC visits will take place within 48 h of request by a client, and we anticipate that the majority of initial visits will occur within the first 2 weeks postpartum. Three self-employed IBCLCs already contracted by the 5Ps program have been recruited to deliver the intervention. Private IBCLC services are not covered by provincial health insurance in Ontario, so women who use this resource are typically of higher socio-economic status. The 5Ps staff previously screened many self-employed IBCLCs to select those who practice with a client-centred approach and are able to adapt to the circumstances of vulnerable women, such as communicating through interpreters and visiting low-income homes.

The first home visit will last approximately 1.5 h and include assessment, education and management of the client’s lactation concerns. In-person or telephone interpreters will be provided for clients with limited English fluency. The IBCLC conducting the visit will provide her contact information to the client for follow up contact by text, phone or email. Following the first home visit, the Research Coordinator will contact the client to see if they were satisfied with the service and arrange a second visit with the IBCLC if needed. In cases with more complex lactation issues, a third visit may be offered. Follow up visits are expected to be approximately 1 h in length.

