The Infant Feeding Questionnaire has been professionally translated into Chinese and back-translated by a second translator. We will utilize published Spanish translations of the Infant Feeding Intentions [38] and Prenatal Breastfeeding Self-Efficacy Scale [44]. Translations into Chinese, Spanish and Portuguese were accessed from a compilation of validation studies for the EPDS [45] and were provided by [name] for the Breastfeeding Self-Efficacy Scale-Short Form and by MindGarden, Inc. for the STAI. Other study forms have been translated into Chinese by our Research Assistant or will be orally translated at the time of data collection by professional interpreters.

In order to monitor feasibility of implementation delivery, the Research Coordinator will track the number of clients eligible for the intervention, the number who participate (defined as receiving at least one IBCLC visit), and the specific services provided (number of home visits and breast pump provision, if applicable). Reasons for clients not accessing the intervention will also be recorded. The IBCLCs will complete a data collection form after each home visit, recording the assessment components covered, concerns identified and services provided. These data will be analysed to determine reach, uptake and fidelity of the intervention delivery.

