### Statistical analysis

Descriptive statistics will be generated for all variables. Primary and secondary outcome measures will be compared between the pre- and post-intervention groups using t-tests for continuous variables and chi-square statistics for categorical variables. Sub-group analysis will be performed to examine differences in outcomes based on the effect modifiers (program site, parity, food security status and intervention participation) as shown in the conceptual model (Fig. 1). Logistic regression analysis will be used to determine the relationship between breastfeeding self-efficacy scores at 2 months postpartum and breastfeeding practices at 4 and 6 months postpartum, controlling for confounders. All statistical analysis will be performed using IBM SPSS Statistics for Windows, version 26 (IBM Corp., Armonk, N.Y., USA).

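### Intervention participation is listed as an effect modifier, but it is post-birth uptake that can occur only in the post phase, so it cannot define a sub-group of the pre/post effect

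*Protocol article*

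**What the plan says.** The Statistical analysis section names four variables for sub-group analysis and classes all of them as "effect modifiers (program site, parity, food security status and intervention participation", with reference to the conceptual model in Fig. 1 (not shown).

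The Data collection section fixes what participation means when it describes monitoring: "the number who participate (defined as receiving at least one IBCLC visit". The Intervention description section limits who can have a visit: clients "who give birth during the intervention period and live in the city of Toronto will have access to in-home lactation support from an IBCLC". On timing it states: "This service will be offered pro-actively in the early postpartum period, but will be available throughout the first 6 months".

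The same section describes two routes to a visit. One is self-referral: "Clients will be encouraged to contact the Coordinator if they need lactation support". The other is a call from the project: "the Coordinator will also pro-actively telephone interested clients around the time of birth to offer the IBCLC support".

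The main contrast is defined by date of birth, not by receipt of a visit. Under Study design and hypothesis, outcomes are "compared between participants who give birth before and after initiation of the lactation support intervention", and the hypothesis concerns women who have access to the service. In what follows, a user is a post-phase woman with at least one visit.

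**The concern.** An effect modifier of a pre/post effect has to be a characteristic that women in both phases can have and that the intervention does not itself determine. Site, parity and prenatally measured food security meet this. Receipt of a visit does not, because it is part of the intervention.

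If the analysis is run as listed, what comes out is a comparison of women who used the service with women who did not, or with all women from before the service existed. These are different kinds of women. The Background section says why this matters for the outcome: "Two key contributors to both early cessation and non-exclusive breastfeeding are the perception of insufficient breastmilk supply and unresolved breastfeeding difficulties". Difficulty with feeding is thus a reason to seek a visit and also a cause of not breastfeeding exclusively. Interest in the service pulls the other way, because keen women are more likely to accept it and more likely to continue.

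The stake is a secondary result presented as a sub-group effect whose sign could reflect only who chose to use the service. The study is meant to guide how lactation support is built into the national programme, so a misleading figure by uptake would have a consequence.

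**Working it through.** **The plan's own figure.** The only stated calculation is the sample size: 53% against 73%, power 0.80, alpha 0.05 (two-sided assumed). With pooled variance and no continuity correction, n = [1.96·√(2·0.63·0.37) + 0.8416·√(0.53·0.47 + 0.73·0.27)]² / 0.20² = 90.3, so 91 per group against 93 stated. Allowing for attrition, 93/0.90 = 103.3, so 104 against 105 stated. The figures reproduce to within two women, and the point here does not bear on them.

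**Can the sub-group effect be estimated?** Cross phase with participation:

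- Pre phase, user: empty by design, since access requires birth in the intervention period.
- Pre phase, non-user: the whole pre group.
- Post phase, user and non-user: both occupied.

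With one of the four cells empty, there is no pre/post difference among users and no interaction term. The pre-phase women who would have used the service cannot be told apart from those who would not.

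**How far can the remaining contrasts mislead?** The documents give no uptake rate and no rate of difficulties, so the following inputs are assumptions, apart from the 53%:

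- overall exclusive breastfeeding at 4 months of 53% (Sample size section), with no true intervention effect;
- a share q of women with early difficulties, 30% or 50%;
- a gap g of 10, 20 or 30 points in exclusive breastfeeding between women without and with difficulties, so the rate without is b = 0.53 + q·g and the rate with is a = b − g;
- uptake u1 with and u0 without difficulties. Need dominates: 80/40, 70/30 or 90/50%. Motivation dominates: 40/60%. Unrelated: 50/50%.

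Formulas:

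- Users: [q·u1·a + (1−q)·u0·b] / [q·u1 + (1−q)·u0]
- Non-users: [q·(1−u1)·a + (1−q)·(1−u0)·b] / [1 − q·u1 − (1−q)·u0]

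Example with q = 0.5, g = 0.20, uptake 80/40: b = 0.63, a = 0.43. Users: (0.172 + 0.126)/0.60 = 49.7%. Non-users: (0.043 + 0.189)/0.40 = 58.0%. The difference is −8.3 points, and −3.3 points against the pre group's 53%.

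The scenarios that set the limits, with this example:

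| q | g (points) | uptake with/without difficulties | users | non-users | users − non-users | users − pre |
|---|---|---|---|---|---|---|
| 0.3 | 10 | 80/40 | 51.4% | 54.8% | −3.4 | −1.6 |
| 0.3 | 10 | 90/50 | 51.6% | 55.2% | −3.6 | −1.4 |
| 0.5 | 20 | 80/40 | 49.7% | 58.0% | −8.3 | −3.3 |
| 0.5 | 30 | 70/30 | 47.0% | 59.0% | −12.0 | −6.0 |
| 0.5 | 30 | 90/50 | 48.7% | 63.0% | −14.3 | −4.3 |
| 0.3 | 10 | 40/60 | 53.8% | 52.1% | +1.7 | +0.8 |
| 0.5 | 30 | 40/60 | 56.0% | 50.0% | +6.0 | +3.0 |
| any | any | 50/50 | 53.0% | 53.0% | 0 | 0 |

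**Timing.** The service is open for 6 months and the primary outcome is taken at 4 months. A woman whose first visit falls in month 5 counts as a user after her outcome is already fixed. A visit prompted by feeding that is already failing puts the outcome process before the exposure.

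**The case against.** The strongest reply is about weight. The access comparison comes first in the Study design, Statistical analysis and Discussion sections, and nowhere is receipt of a visit presented as the effect of interest. Participation is one of four sub-group variables. The article specifies no interaction test, says only that differences in outcomes will be examined, and may leave adjustment to a fuller plan. It already places uptake under feasibility and already concedes that the design is weaker than a randomised trial. Most first visits are expected within 2 weeks of birth, so few should come after month 4.

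Most of this stands, and it sets the severity. What it does not remove is the classification. The text itself calls participation an effect modifier, and no later detail can make that estimable. The point does not rest on any missing statement about adjustment.

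Three stronger readings are tempting, and the documents support none of them.

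- A reader might infer that the main result is compromised. It is not: the groups are defined by date of birth, whatever the uptake.
- A reader might infer that the visits are bound to look harmful because need drives uptake. The telephone route goes to interested clients, so the sign cannot be fixed in advance.
- A reader might infer a bias of half the planned 20-point effect. A single scenario (half with difficulties, 40% against 66% exclusive breastfeeding, uptake 80/40) does give 0.292/0.60 = 48.7% against 0.238/0.40 = 59.5%, or −10.8 points. But those inputs are assumed, that contrast is within the post phase, and against the pre group the same inputs give 48.7 − 53 = −4.3 points.

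**Conclusion.** The point holds as a should-fix. Listing intervention participation as an effect modifier is wrong as written, because the characteristic is determined after birth and is absent from the pre group by design. That part follows from the text and needs no assumed number.

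The size of the bias in the substitute contrasts does rest on assumptions, namely the grid of difficulty rates, prognostic gaps and uptake patterns shown above. It supports the statement that the bias could be material and of either sign. It does not support any single estimate. The bias is zero only if uptake is unrelated to prognosis, which the article's own account of difficulties and of the routes to a visit makes unlikely.

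**What to change.** In the Statistical analysis section and the conceptual model, delete intervention participation from the effect modifiers and sub-groups. State that every post-phase woman is analysed in the post group whatever her uptake, and report uptake with the reach and fidelity results, where it is already planned.

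If outcomes by uptake are wanted, define a separate exploratory analysis and label it observational. Adjust it for the covariates already available before birth: feeding intentions, prenatal self-efficacy, parity, socio-demographics, food security and site. Count only visits made before the outcome time point. Say that confounding will remain, because difficulties arising after birth are not captured by prenatal covariates, and the visit forms record concerns only for women who were visited.

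Do not use phase as an instrument to obtain an effect among users. The consultants' group workshops in the intervention phase also teach how to establish breastfeeding, so phase can act without a visit. Phase is also not randomised, so any calendar trend would be divided by uptake and enlarged (at an assumed 60% uptake, by 1/0.6 = 1.67).

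The cost is a sentence or two in the analysis section and one change to the figure. No data collection changes, and the sample size stays as it is.

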### Sample size

The sample size estimate is based on the primary outcome. Preliminary data indicated that 53% of program clients were exclusively breastfeeding at 4 months postpartum. Based on an anticipated increase to 73% in the post-intervention group, we require 93 women per group in order to achieve 0.80 power with alpha = 0.05. To allow for 10% attrition we aim to recruit 105 women per group for a total of 210 study participants. The anticipated attrition rate is based on preliminary evidence of high retention in a separate prospective infant feeding study conducted by our group at another CPNP site.

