### Data collection

Data will be collected in person or by telephone either by AM or by a Mandarin speaking Research Assistant. Professional interpreter services will be used as required for other non-English speaking participants.

All primary and secondary outcome measures will be assessed through prospective data collection using a standardized and validated Infant Feeding Questionnaire developed by [name]’s research group and used in several prior research studies at the Hospital for Sick Children in Toronto [35]. This questionnaire will be administered to study participants at 2 weeks postpartum, and then monthly until 6 months for a total of seven infant feeding data collection points (Table 1). At each time point, participants will be asked to report the average number of daily milk feeds their infant received in the past 2 weeks, divided into feeds at the breast, expressed breastmilk feeds, and formula feeds. Provision of cow’s milk, non-milk fluids and vitamin or mineral supplements will also be recorded. Participants who stop breastfeeding will be asked for the last date breastmilk was provided and the main reasons for cessation. If applicable, the date of solids introduction and the name of the first food will be recorded.

**Table 1 Tab1:** Data collection timeline

Study Instrument	Prenatal	Postnatal Data Collection						
		2 weeks	1 month	2 months	3 months	4 months	5 months	6 months
Maternal Socio-demographics Questionnaire	√							
Infant Feeding Intentions Scale	√							
Prenatal Breastfeeding Self-Efficacy Scale	√							
Household Food Security Questionnaire	√							√
Breastfeeding Self-Efficacy Scale-Short Form		√		√				
Infant Feeding Questionnaire		√	√	√	√	√	√	√
Edinburgh Postnatal Depression Scale				√				
State-Trait Anxiety Inventory for Adults				√				
Six Months Postpartum Questionnaire								√

We hypothesize that the intervention effects will be mediated through increases in breastfeeding self-efficacy, which will be assessed at 2 weeks and 2 months postpartum using the Breastfeeding Self-Efficacy Scale-Short Form [36]. Additional data collection tools are listed below. The Socio-demographics and 6 Months Postpartum questionnaires were developed for this study, with income-related questions drawn from Statistics Canada’s Employment Insurance Coverage Survey [37]. The remaining instruments are validated scales from the literature, all of which have been used previously with vulnerable populations.

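### The mediation hypothesis rests on two separate analyses, and no phase-adjusted model or indirect effect joins them into a test of mediation

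*Protocol article*

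**What the plan says.** Mediation is stated twice. Study design and hypothesis says of the effect on exclusive breastfeeding at 4 months that "this effect will be mediated by higher breastfeeding self-efficacy scores". Data collection says: "We hypothesize that the intervention effects will be mediated through increases in breastfeeding self-efficacy, which will be assessed at 2 weeks and 2 months postpartum".

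Two planned pieces of work use the postpartum scores:

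- Study design and hypothesis says that "breastfeeding self-efficacy scores will be compared between participants who give birth before and after initiation of the lactation support intervention". The Discussion restates this as an expectation of higher scores at 2 months in the group with access to the intervention.
- Statistical analysis plans a logistic regression to "determine the relationship between breastfeeding self-efficacy scores at 2 months postpartum and breastfeeding practices at 4 and 6 months postpartum", "controlling for confounders".

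The confounders are not listed in the text, and the conceptual model (Fig. 1) is not visible in the copy reviewed. The section's group tests are described as follows: "Primary and secondary outcome measures will be compared between the pre- and post-intervention groups using t-tests for continuous variables and chi-square statistics". Self-efficacy is not among the listed primary and secondary outcomes, so the score comparison is stated only in the design section.

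**The concern.** A claim of mediation needs three things: the intervention changes self-efficacy, self-efficacy predicts feeding among women in the same study phase, and an estimate of how much of the effect passes through the score. The protocol plans the first. For the second it plans an association in which phase is not named. It does not plan the third.

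The risk is in interpretation. The Background already treats high self-efficacy as favouring continued breastfeeding, so a positive regression is likely whatever the intervention did. If that result is read beside a pre/post difference in scores, it could be reported as support for the proposed mechanism. Yet the intervention has a plausible route that bypasses confidence, because breast pumps are provided as practical support. A design that moves score and feeding separately would then look like mediation.

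There is a second weakness. By 2 months some women may have stopped exclusive breastfeeding and may report lower confidence for that reason. Part of the association between the 2-month score and later feeding would then run from feeding to score.

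**Working it through.** **The plan's own figure.** Inputs from Sample size: 53% and 73%, alpha 0.05 (taken as two-sided), power 0.80. The pooled-variance formula is

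n = [1.960·√(2·0.63·0.37) + 0.842·√(0.53·0.47 + 0.73·0.27)]² / 0.20² = (1.338 + 0.562)² / 0.04 ≈ 90.3, so 91 per group.

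The stated 93 is reproduced to within 2, and power at 93 is 0.81. Nothing below changes this figure.

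**Simulation settings.** There are 93 women per phase (186 in all) and 1,000 runs per scenario, and the score has SD 1. The model is

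- score = a·phase + noise
- logit P(exclusive at 4 months) = ln(0.53/0.47) + c·phase + b·score

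The 93 and the 53% come from the protocol. The values of a, b and c are assumptions. For scale, the protocol's 53% to 73% is a log odds ratio of ln(0.73/0.27) − ln(0.53/0.47) = 0.995 − 0.120 = 0.87, so c = 0.9 is close to the planned effect acting wholly outside the score.

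**Percentage of runs with p < 0.05**

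| Scenario | Score by phase | Feeding on score, no phase | Both phase-to-score and score-to-feeding given phase |
|---|---|---|---|
| 1. No mediation: a=0, b=0.8, c=0.9 | 5.3 | 99.6 | 5.3 |
| 2. No mediation: a=0.5, b=0, c=0.9 | 91.3 | 9.1 | 4.6 |
| 3. No mediation: a=0.8, b=0, c=0.9 | 99.8 | 19.0 | 5.2 |
| 4. Mediation: a=0.5, b=0.8, c=0.5 | 93.4 | 100 | 93.0 |

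**Reading both planned pieces together.** The protocol gives no rule for combining them. The generous reading requires both to be significant. The joint rate then lies between P₁ + P₂ − 1 and the smaller of P₁ and P₂:

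- Scenario 1: between 0.053 + 0.996 − 1 = 4.9% and 5.3%. The score comparison protects the conclusion.
- Scenario 2: between 0.913 + 0.091 − 1 = 0.4% and 9.1%.
- Scenario 3: between 0.998 + 0.190 − 1 = 18.8% and 19.0%, against 5.2% once phase is in the second model.

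So the pre/post comparison covers the case where the intervention does not move self-efficacy. It does not cover the case where the intervention moves score and feeding by separate routes. A phase term does.

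**Feeding status driving the score.** Assume 65% are exclusive at 2 months, 53% overall are exclusive at 4 months (all from that 65%), phase has no effect, and the score has no causal effect but is higher in women still exclusive. The regression is significant in about 97% of runs if the gap is 0.8 SD and about 70% if it is 0.5 SD. The 65% and both gaps are assumptions. Adding phase does not remove this problem, which comes from the timing of the score.

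**The case against.** The strongest reply is that both steps of the mechanism are in the protocol. The design section compares scores between phases, and the regression links score to later feeding. The regression is described only as a relationship and is never called a mediation test. The confounders are unlisted, so phase could be among them. An article may leave covariate lists and indirect-effect estimation to a fuller document.

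Much of this stands, and it rules out some stronger readings that a reader might infer:

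- *That the regression is the only planned use of self-efficacy, or that the plan could never contradict mediation.* The pre/post comparison could. If the intervention left scores unchanged, that comparison would be significant in only about 5% of runs.
- *That false support would arise in nearly every trial.* The rates near 100% describe the regression taken alone, under assumed effects.
- *That phase is definitely left out.* The text does not name it. That is all that can be said.
- *That the 2-month score is the wrong choice.* The Discussion states the hypothesis at 2 months. The 2-week score has its own drawback: only most initial visits are expected by then, follow-up visits come later, and that assessment has a window of 7 days either side.

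What the reply does not answer is the mismatch in what is written. The article specifies predictor, outcomes and time points for the regression, and this model does not match the hypothesis it would be read against. Even if phase were among the confounders, the article plans no indirect or direct effect.

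**Conclusion.** The point holds in a limited form. The mediation clause of the hypothesis is not tested by the analyses as described, because the score comparison and the regression are not joined by a phase-adjusted model and no indirect effect is estimated. The regression alone can be strongly positive with no mediation. Without phase it can also pick up an association created by the intervention acting on score and feeding separately: 9% to 19% significant in the two assumed scenarios, against about 5% with phase.

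These rates depend on assumed effect sizes and are illustrative only. The conclusion about the model rests on the text naming no phase term and on the absence of any planned indirect effect. The matter concerns a secondary, mechanistic claim. It leaves the primary comparison and the sample size untouched, but should be settled before the data are analysed.

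**What to change.** Add a secondary mediation analysis with two models:

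- (a) self-efficacy on study phase, adjusted for prenatal self-efficacy and prespecified baseline confounders;
- (b) exclusive breastfeeding at 4 months on study phase, self-efficacy and the same covariates.

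Report the indirect and direct effects with bootstrap 95% confidence intervals. Use the 2-month score as hypothesised. Repeat with the 2-week score as a sensitivity analysis, noting that it may precede some of the support. Acknowledge that the 2-month result may partly reflect feeding status by then. State that the existing regression describes an association and will not be reported as support for mediation.

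The cost is wording and some programming. Phase, prenatal self-efficacy and both postpartum scores are already collected (Table 1). The drawback is precision: with about 186 women the indirect effect will be estimated imprecisely, so it should be presented as secondary and read from its interval.
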